### Secondary outcomes

The continuous secondary outcome measures at 3 and 6 months will be analysed with the same mixed effects linear regression model; the adjusted mean difference in change in these outcomes will be presented with 95% CIs with no adjustment for multiple testing. Ordinal outcomes will be analysed using an ordinal logistic regression model to assess the shift in the distribution of scores at follow-up that is attributed to treatment. The proportion of participants achieving at least 6 points improvement in ULFM total motor score (at 3 and 6 months) compared with baseline will be analysed using a mixed effects logistic regression model adjusted for fixed covariates (baseline ULFM scores, age and sex) and site (random effect). Adjusted difference in proportions between each tVNS compared with the control, with associated 95% CIs, will be postestimated via margins.

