### Sample size justification and interim analysis

Rehabilitation alone has been shown to improve the ULFM total motor score by around 3 points^17^; an improvement of 6 points is considered the minimal clinically important difference (MCID).^22^ The active treatment group would need to improve the ULFM by 3 points more than sham tVNS and rehabilitation to be clinically meaningful. The trial will require 228 participants in total (76 per group) with ULFM outcome at 3 months. An interim analysis for treatment selection will be performed when 114 participants in total (38 per group) have accrued ULFM outcome at 3 months. This assumes a 1:1:1 allocation ratio, 85% marginal power and 2.5% one-sided family-wise type I error. We expect a 6% dropout rate,^16^ so the initial sample size is inflated to 243 participants (81 per group). However, this dropout rate will be re-estimated at an interim analysis, and the sample size adjusted accordingly to achieve 228 participants with primary outcome data. We chose a treatment selection rule to minimise the risks of dropping potentially effective tVNS treatments or selecting ineffective treatments at an interim analysis. A tVNS treatment will be selected to progress to stage 2 if the test statistic is >0.792 (corresponding to a 1-point ULFM mean difference in change compared with a shared control arm; 0.18 of the expected SD of 5.5^11^ and one-third of our targeted MCID). Such a small effect observed halfway through the trial will be very unlikely to improve close to or beyond our targeted MCID even if the treatment is carried forward until the end. Thus, we will drop a tVNS treatment early if it fails to demonstrate an effect of>1/3 of the MCID. At the end of stage 2, a treatment will be declared efficacious if the test statistic is above 2.176—chosen to guarantee that the chance of incorrectly rejecting at least one null hypothesis is controlled at 2.5% (one-sided tests).^23^ See Section 11.1 of the protocol for details on sample size with rationale and aspects of interim analysis including adaptation decision rules with rationale and operating characteristics of the adaptive design.

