### Statistical analysis

Details of all statistical analysis methods relating to the interim and final (stage 2) analyses will be documented in an open-access and prespecified statistical analysis plan before accessing unblinded data. Interim and final (stage 2) analyses for efficacy will be based on a modified intention-to-treat population—all randomised participants who have outcome data regardless of non-compliance, protocol deviations or withdrawals. Sensitivity analysis will be performed on the per-protocol population—all randomised participants who adhered to treatment with no major protocol deviations. Adherence is defined as completing 40/60 therapy sessions for at least 30 min per session (all groups) and completing at least 1 hour of tVNS with activities of daily living (ADLs). Safety population will include eligible participants with informed consent, and analysis will be based on the treatment they received. Reporting will adhere to the Adaptive Designs Consolidated Standards of Reporting Trials Extension.^24^

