### Primary outcome

The primary outcome (change in ULFM total motor score at 3 months) will be analysed using a mixed effects linear regression model adjusted for fixed effects covariates (baseline ULFM score, age AND sex) and site (random effect). Treatment effects will be presented as the adjusted mean difference in change with multiplicity-adjusted CIs and associated p values. Subgroup analyses will be undertaken to explore the effect of important variables related to the participant and their treatment on the primary outcome. These subgroups are:

Age (≤6, >60 years).Baseline ULFM score (20–35, 36–50).Biological sex at birth (male, female).Side of hemiparesis (left, right).Time since stroke (<12 months, >12 months).Baseline mNIHSS score (0–4=minor, 5–20=moderate and 21–31=severe).

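### As written, continuous secondary outcomes other than the ULFM motor score are adjusted for baseline ULFM but not for their own baseline, at a modest and avoidable cost in precision

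*Protocol article*

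**What the plan says.** In the protocol article, the Primary outcome section specifies a mixed effects linear regression for change in ULFM total motor score, "adjusted for fixed effects covariates (baseline ULFM score, age AND sex) and site (random effect". The baseline term is named as ULFM; it is not described generically as the baseline value of whichever outcome is analysed.

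The Secondary outcomes section then makes three statements:

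- Continuous outcomes: "The continuous secondary outcome measures at 3 and 6 months will be analysed with the same mixed effects linear regression model", and "the adjusted mean difference in change in these outcomes will be presented with 95% CIs with no adjustment for multiple testing".
- Ordinal outcomes: "Ordinal outcomes will be analysed using an ordinal logistic regression model to assess the shift in the distribution of scores at follow-up". No covariates are listed.
- The 6-point ULFM responder outcome: a "mixed effects logistic regression model adjusted for fixed covariates (baseline ULFM scores, age and sex) and site (random effect".

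The Identification and recruitment section has eligible participants complete the remaining outcome assessments before they are randomised, so own-baseline values will be available. The Randomisation section lists the minimisation factors as age, baseline ULFM, sex and site. The Statistical analysis section leaves the full methods to a separate document, which is not shown: "Details of all statistical analysis methods relating to the interim and final (stage 2) analyses will be documented in an open-access and prespecified statistical analysis".

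**The concern.** In the primary analysis, baseline ULFM does two jobs: it is a minimisation factor and it is the outcome's own baseline. When the same covariate list is carried over to, say, the Wolf Motor Function Test or the stroke-specific quality-of-life score, it does only the first. The outcome's own baseline, usually its strongest predictor, is subtracted when change is formed but does not enter as a covariate. Subtraction fixes the baseline slope at 1, whereas regression estimates it. When the true slope is below 1, the change score carries avoidable noise and over-corrects for chance baseline differences.

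At stake is the precision of the estimates for secondary objective (b), the outcomes other than arm motor impairment. Minimisation does not balance these outcomes' own baselines except through their correlation with ULFM, age, sex and site.

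**Working it through.** **The plan's own figures.** The article gives no figure for the secondary outcomes. Its primary-outcome figures reproduce and are not touched by this point:

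- Interim threshold for a 1-point difference: 1/(5.5 × √(2/38)) = 0.7925 (stated 0.792).
- Marginal power with 38 then 76 per group, difference 3, SD 5.5: P(Z₁ > 0.792, Z₂ > 2.176), with means 3/(5.5√(2/38)) = 2.378 and 3/(5.5√(2/76)) = 3.362 and correlation √(38/76), gives 86.1% (stated 85%).
- Family-wise error with the selection rule applied, 4 million simulated trials: 0.0250 (stated 2.5%).
- Dropout: 228/0.94 = 242.6, rounded up to 243 (as stated).

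**Inputs for the check.** From the article: 76 per group with outcome ("The trial will require 228 participants in total (76 per group) with ULFM outcome at 3 months"). Assumed, because the article gives neither: ρ, the correlation of an outcome's own baseline with its follow-up value, from 0.5 to 0.9; and r, the correlation of that own baseline with baseline ULFM, from 0 to 0.7. SD is set to 1 at both visits. Baseline ULFM is taken to relate to follow-up only through the own baseline. Age, sex and site are left out of both models.

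**Precision.**

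- Change adjusted for baseline ULFM only: residual variance = 2(1 − ρ) − [r(1 − ρ)]².
- Change adjusted for own baseline: residual variance = 1 − ρ².

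Example at ρ = 0.5, r = 0: 2(0.5) − 0 = 1.00 against 1 − 0.25 = 0.75; ratio 1.33; SE ratio √1.33 = 1.155. At r = 0.7: 1.00 − (0.35)² = 0.8775; ratio 1.17; SE ratio 1.082.

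| ρ | Variance ratio (r = 0.7 to r = 0) | SE excess |
|---|---|---|
| 0.5 | 1.17 to 1.33 | 8.2% to 15.5% |
| 0.7 | 1.09 to 1.18 | 4.4% to 8.5% |
| 0.9 | 1.03 to 1.05 | 1.3% to 2.6% |

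**Chance imbalance.** One standard error of the difference in own baseline between two groups of 76 is √(2/76) = 0.162 SD. A change score passes on −(1 − ρ) of it:

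- ρ = 0.5: −0.5 × 0.162 = −0.081 SD
- ρ = 0.7: −0.3 × 0.162 = −0.049 SD
- ρ = 0.9: −0.1 × 0.162 = −0.016 SD

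These take r = 0. With r above 0, the ULFM term absorbs part of the imbalance. Over repeated randomisations the imbalance averages to zero, so there is no expected bias.

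**Where the point does not apply.** For ULFM motor score at 6 months, and for the 6-point responder analysis, baseline ULFM is the outcome's own baseline. Secondary objective (a), whether the reduction in arm motor impairment is sustained, is therefore unaffected.

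**The case against.** The best reply is that the same model may mean the same structure, with each outcome's own baseline in place of ULFM, and that the unseen analysis plan will say so. That is possible, and the article nowhere states that own baseline is excluded. But the article does more than stay silent here: it names a covariate set with ULFM in it and then applies that model to other outcomes. An analyst who follows the text would fit the wrong baseline term. A correction of wording is therefore fair, while a charge of a settled error is not.

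A reader might go further and infer three things that the documents do not support.

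- **That chance imbalance is left uncorrected in the continuous outcomes.** It is not. The reported quantity is a difference in change, so own baseline is already subtracted and only the residual shown above remains. Regression to the mean acts on all randomised groups alike in expectation.
- **That the ordinal analyses are unadjusted.** The article lists no covariates for them and does not say there are none. The contrast with the neighbouring logistic model may be uneven condensation, and such lists are commonly left to the analysis plan. If the models truly had no baseline term, the loss would be larger. In a simulated five-category outcome with 76 per group and an assumed latent effect of 0.4 SD (250 runs per setting), power was about 66%, 65% and 69% without the baseline score and 76%, 86% and 98% with it, at ρ of 0.5, 0.7 and 0.85. That is a reason to settle the wording, not evidence of a flaw.
- **That particular mood, fatigue or daily-living scales are affected.** The article does not say which scales are treated as continuous and which as ordinal.

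It is also fair to object that the size rests on assumed correlations. The article's own description of a more stable deficit after 6 months makes high ρ plausible for motor measures, which puts those nearer the bottom of the range.

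**Conclusion.** The point holds for continuous secondary outcomes other than the ULFM motor score. As written, their model omits the outcome's own baseline as a covariate. The consequence is mainly a loss of precision: a standard error about 1% to 15% larger than with own-baseline adjustment, for assumed ρ from 0.9 to 0.5 and r from 0.7 to 0. The loss would be greater for a scale with weaker baseline to follow-up correlation and smaller for a stronger one. The secondary intervals carry no multiplicity adjustment, so no error-rate claim depends on them. The ordinal part is a request for clarification only. Overall this is a free improvement of minor severity.

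**What to change.** In the analysis plan, and in the protocol text when next amended, state that each continuous secondary model includes that outcome's own baseline value as a covariate, in addition to baseline ULFM, age, sex and random site. Keep baseline ULFM because it is a minimisation factor; where the outcome is the ULFM motor score, the two baseline terms are one and the same. With own baseline in the linear model, the treatment estimate is identical whether change or the follow-up score is the response, so the planned reporting as a difference in change can stay.

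As a minor clarification, add that each ordinal model includes the outcome's baseline score together with baseline ULFM, age, sex and site.

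The cost is a sentence or two of wording. No new data are needed for outcomes assessed at the baseline visit, and the sample size and interim rules do not change. The wording should be settled before unblinded data are accessed, which is the timing the article already sets for its analysis plan.

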### Safety monitoring and reporting

AEs and SAEs are defined as events that occur between randomisation and completion of their 6-month follow-up. These may be identified by the participant, research nurse, therapist or any other individual at any point in the trial. AEs will be recorded on the AE report form within the participant CRF. Some expected AEs include those known to be associated with tVNS and/or rehabilitation, including skin irritation, headache, nausea and limb pain.^25^ In a recent systematic review of auricular tVNS, no adverse cardiac events were reported in 484 212 min-days of stimulation.^26^ SAEs will be reported to the CTRU immediately and within one working day from identification. Unexpected SAEs related to the intervention will be reported to the research ethics committee within 15 working days. AEs and SAEs will be reviewed by the DMEC and TSC regularly.

### Mechanistic substudy

Participants willing to travel to the central site (Sheffield) and with no contraindications for an MRI scan will be invited to participate in the mechanistic substudy and provide written informed consent. The aim of the substudy is to establish whether active tVNS paired with rehabilitation enhances cortical plasticity, cerebral blood flow and metrics of brain oxygen metabolic profiles or reduces systemic inflammation compared with sham tVNS with rehabilitation therapy. It will also explore whether this is associated with improvement in upper limb function and whether baseline features of the MRI such as lesion size, location or the presence of white matter ischaemic changes are predictors of the response to active tVNS. Up to 40 participants will have a 60-min multimodal MRI scan (T1, T2, Diffusion Tensor Imaging (DTI), Fluid Attentuated Inversion Recovery (FLAIR), Arterial Spin Labeling (ASL), task and resting state functional MRI (fMRI)) at baseline (within 4 weeks of baseline measure assessments and prior to commencing the tVNS/therapy programme) and at 3 months. Up to 20 of these participants will also have an 18F-fluorodeoxyglucose positron emission tomography (18F-FDG-PET) scan concurrent to the multimodal MRI. Briefly, the task fMRI paradigm consists of a block design with 3×30 s blocks of active flexion-extension movements of either the affected or unaffected fingers, wrist or elbow at 1 Hz (six movement tasks) interspersed with 30 s rest blocks. Preprocessing of the functional MRI results will include an analysis pipeline of stroke lesion segmentation, motion correction, slice timing correction, coregistration to structural MRI, normalisation to a shared template and smoothing with a Gaussian kernel. A general linear model will be applied to identify task-related activation compared with the rest. First-level individual participant contrasts will be generated, and second-level analysis will compare activations postintervention versus preintervention in active versus sham treatment groups. Correction for multiple comparisons will be applied via family-wise error or false discovery rate correction. Region of interest analysis will be carried out in relevant sensorimotor areas including the primary motor cortices, supplementary motor areas, premotor cortex and primary somatosensory cortex. Analysis will be carried out in the latest version of statistical parametric mapping.^27^ Up to 40 participants will have blood samples collected at baseline and 3 months for serum analysis of systemic inflammatory cytokines including interleukin 1 alpha, tumour necrosis factor alpha and interferon gamma. Blood samples will be centrifuged and the supernatant stored at −70°C for future analysis.

### Ethics and dissemination

This study has received ethical approval from the Cambridge Central Research Ethics Committee (12/10/2022, REC reference: 22/NI/0134) and is registered as a clinical trial (ISRCTN20221867). The study sponsor is Sheffield Teaching Hospitals National Health Service Foundation Trust. The trial will be conducted in accordance with this protocol and the International Council for Harmonisation's Good Clinical Practice guideline. Important protocol modifications (eg, changes to eligibility criteria, outcomes and analyses) will be communicated to relevant parties including oversight committees, funders, investigators, Research Ethics Committe (REC), Health Research Authority (HRA) and trial registries.

Data confidentiality as per the Data Protection Act 2018 will be followed. Trial participants will be provided with a unique study ID number, and all relevant data will be entered into the password-protected and restricted Sheffield CTRU in-house electronic data management system. Access will be granted to authorised representatives from the sponsor, host institution and regulatory authorities for audit and monitoring purposes.

Any significant modifications to the protocol, for example, those that impact study procedures, study design, eligibility criteria or participant safety will require a formal amendment to the protocol. This will be agreed on by the TSC, funder and ethics committee before implementation and notification of health authorities.

The results of the clinical trial will be disseminated through peer-reviewed scientific journals, at clinical and academic medical and rehabilitation conferences and to trial participants and patient groups. A summary of the research will be made available on the University of Sheffield CTRU website.

Requests for patient-level data and statistical code should be made to the corresponding author and will be considered by members of the original TMG, including the chief investigator and members of CTRU, who will release data on a case-by-case basis. Data will be shared following the principles for sharing patient-level data as described by Smith *et al* (2015). The data will not contain any direct identifiers; we will minimise indirect identifiers and remove free-text data to minimise the risk of identification.

## Data Availability

Data are available upon reasonable request.
